**Principal Investigator:**

[name]

[name]

[name]

1. **PURPOSE OF THE STUDY AND BACKGROUND**
   1. **Purpose of the study**
      1. Characterize baseline status and disease progression over two years in 500 DM1 patients with myotonic dystrophy type 1 (DM1). Selected functional tests and patient-reported outcomes will be assessed for ability to quantify disease burden, detect disease progression, and predict changes.
      2. Optimize sample collection and analysis procedures for use of muscle RNA alternative splice events as biomarkers of DM1 severity. This analysis will be carried out on a subset of 60 participants who will undergo two muscle biopsies 3 months apart.
      3. Identify genetic modifiers of DM1 severity by performing a genome-wide association (GWA) study.
   2. **Background**

Mechanistic studies of DM1 have revealed a novel RNA-mediated disease process. The field has reached consensus that RNA toxicity is the core mechanism for DM1 pathogenesis. Good molecular targets have been identified, and recently there has been rapid progress in developing targeted therapies. Studies have shown that RNA toxicity is reversible in mouse models, encouraging us to believe that targeted treatments may have transformative effects on DM1 patients. However, recent meetings of stakeholders, including representatives from FDA, industry, academia, and advocacy, have indicated that three obstacles stand in the way of capitalizing on this opportunity: (1) insufficient data on natural history; (2) lack of reliable biomarkers; and (3) incomplete characterization and limited biological understanding of the phenotypic heterogeneity of DM1.

Building on previous work of the Myotonic Dystrophy Clinical Research Network (DMCRN), the present study seeks to overcome these roadblocks. Previously we used long study visits and extensive data collection to assess small cohorts of patients (80 subjects in the first study, 113 in the next). In the current study we are transitioning to focused data collection on a larger cohort. This will expand the scope of natural history data and help us develop strategies for managing patient heterogeneity going forward. For example, we hope to identify clinical measures or patient characteristics that predict future disease progression. In addition, we have made substantial progress in developing biomarkers of DM1 severity and therapeutic response, based on RNA alternative splicing in muscle tissue. We carried out large discovery studies to comprehensively identify DM1-associated splicing defects, then we developed high-throughput assays, and now we are examining test-retest reliability and associations with neurologic impairment. Although in studies to date the splicing biomarkers exhibited good reliability, we observed unexpected variance in some patients. Accordingly, the current study will examine strategies to improve the reliability by making further refinements in our sample collection and analysis procedures. Finally, we are studying the heterogeneity of DM1, and proposing that severity of disease is modified by common genetic variants. We will examine this possibility by performing GWA analysis in the cohort of 500 patients. If successful, this effort may lead to the identification of new stratification markers and therapeutic targets.

1. **STUDY DESIGN**
   1. **Overview**
      1. Investigators and sites

[name], Houston Methodist Medical Center

[name], Stanford University

[name], University of Utah (co-principal investigator)

[name], Ohio State University

[name], National Institutes of Health

[name], Kansas University Medical Center

[name], University of Florida

[name], University of Rochester (co-principal investigator)

[name], University of Iowa

- 1. **Rationale for Study Design**

Approximately 500 adult patients (18 to 70 years old, inclusive) with DM1 will be enrolled at 9 centers (up to 56 patients will be recruited at each site). No treatment will be administered as part of this study. Patients will receive standard of care as determined by their treating physician. Study visits occur at baseline/0 months, 12 months, and 24 months. Few restrictions are placed on participation in the study because we aim to capture the full spectrum of disease severity. Studies of splicing biomarkers in muscle biopsy samples will be conducted on a subset of 60 participants. These patients will have an additional study visit at 3 months.

1. **CHARACTERISTICS OF THE RESEARCH POPULATION**
   1. **Subject Characteristics**
2. **Number of Subjects:** This study will enroll 500 DM1 participants across 9 sites and 56 subjects will enroll locally at the University of Rochester.
3. **Gender and Age of Subjects:** DM1 has a prevalence rate of approximately 1 per 7,500. There are no expected gender differences. Both men and women will be selected for this study.

Children with DM1 are not included in this project because the pathophysiological basis of congenital and childhood DM1 appears to be mechanistically distinct.

1. **Racial and Ethnic Origin:** Prevalence rates of DM1 in major ethnic populations are not documented within the U.S. However, DM-1 prevalence rates in Africa are much lower than those in Europe and the US1. The demographics of myotonic dystrophy in Monroe County are not known. However, the latest demographics of Monroe County (White 77.0%, Black 16.2%, Hispanic 8.5%, Asian 3.7%, Native American 0.1%) indicate that our area contains minority populations similar to the national distribution (https://www.census.gov/quickfacts/fact/table/monroecountynewyork/PST045216). We have based our recruitment projections to reflect the demographics of Monroe County which closely parallel those of the general U.S. population.

The relative gender and minority balance in the Registry will enable us to more quickly and easily recruit patients to the University of Rochester.

- 1. **Inclusion and Exclusion Criteria**

1. **Inclusion Criteria:**

***Inclusion criteria***:

- Age 18 to 70 (inclusive)
- Competent to provide informed consent
- Clinical diagnosis of DM1 based on research criteria1 or positive genetic test
- *Comment:* The clinical research criteria require myotonia, muscle weakness in a characteristic distribution, and history of similar findings in a first degree relative. Genetic testing confirmed the diagnosis of DM1 in > 99% of individuals who satisfied these criteria.2

***Inclusion criteria for participants in the muscle biopsy sub-study:***

- Of the 60 patients undergoing biceps muscle biopsy, at least half will have at least moderate weakness of elbow flexion, defined as MRC score ≤ 4+. This is in order to obtain a muscle tissue sample in a person more severely affected with myotonic dystrophy. Approximately 10 patients at the University of Rochester will undergo the muscle biopsy.

1. **Exclusion Criteria:**

***Exclusion criteria***:

- Symptomatic renal or liver disease, uncontrolled diabetes or thyroid disorder, or active malignancy other than skin cancer.
- Current alcohol or substance abuse
- Concurrent enrollment in clinical trial for DM1, or participation in trial within 6 months of entry.
- Concurrent pregnancy or planned pregnancy during the course of the study.
- Concurrent medical condition that would, in the opinion of the investigator or clinical evaluator, compromise performance on study measures.
- Note: non-ambulatory participants are not excluded, but are limited to <15% of enrollment.

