- 1. **Alternatives to Participation**

There are no alternatives to participation.

1. **CONFIDENTIALIATY OF DATA AND INFORMATION STORAGE**

The underlying source documents (consent, medical records, and case report forms) for the study are maintained in the study binder for each subject at each site. Study binders are kept in secured areas, accessible only to authorized study personnel.

The study sites and their partner(s) and designee(s), ethics committees, and various government health agencies, including representatives of Biogen Idec, may inspect the records of this study. De-identified data from the study will be shared with the partners of this study for the purpose of planning future clinical studies and trials. Scientists at Biogen Idec will have potential to link deidentified study data with serum, plasma, RNA, and cDNA samples that they receive. Every effort will be made to keep the patient’s personal medical data confidential.

1. **RESEARCH INFORMATION IN MEDICAL RECORDS**

Indicate if any research data will be included in the subject’s medical record (e.g., lab test results, drug assignment, or indication of study participation)

1. **DATA ANALYSIS AND MONITORING**
   1. **Sample Size Determination**

Our sample size is designed to capture a clinically meaningful change in our key endpoints: 30-foot go, grip strength, ADF strength, and supine FVC. In order to estimate a sample size based on the continuous variable of change in time in the 30-foot go, the following assumptions were made to capture precision: a mean change of 0.177 with a standard deviation of 1.00. With an alpha of 0.05 and a two-sided 95% confidence interval, a total sample size of 500 subjects is needed to compare two subgroups of 225 individuals each in the mild DM1 and the more severely affected DM1 groups. This sample size accounts for a 10% drop out rate, as was identified in the prior DMCRN study. This sample size would also allow for computation of sensitivity and specificity of the primary endpoints to discriminate these two subgroups of individuals.

- 1. **Planned Statistical Analysis**

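### The 225 per subgroup for the timed walk allows only for drop-out, not for the non-ambulatory participants whom the protocol admits up to a cap of just under 15%

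*Protocol*

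**What the plan says.** Section 12.1 (Sample Size Determination) names four key endpoints: 30-foot go, grip strength, ADF strength and supine FVC. It sizes the study on the first, "the continuous variable of change in time in the 30-foot go", assuming "a mean change of 0.177 with a standard deviation of 1.00". It concludes that "a total sample size of 500 subjects is needed to compare two subgroups of 225 individuals each", one mild and one more severely affected. On losses it says: "This sample size accounts for a 10% drop out rate, as was identified in the prior DMCRN study". No other loss is mentioned.

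The note at the end of the exclusion criteria in section 3 says that "non-ambulatory participants are not excluded, but are limited to <15% of enrollment". The study design section explains that entry restrictions are few so that the whole range of severity is represented.

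The functional measures section describes the timed walk as a 10-meter test done by walking or running from a standing start, with orthotics and ankle braces allowed, and scored as the seconds taken. It gives no value for a participant who cannot do the test. (Section 12.1 and Appendix 1 call the walk a 30-foot go. Both are walking tests, so this point is the same under either name.)

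**The concern.** The step from 500 to 225 per subgroup uses every enrolled participant and leaves nothing in reserve. The eligibility note allows a group who, as the test is described, cannot supply the measurement on which the study is sized. At the permitted mix of participants, the two statements cannot both hold for the walking endpoint.

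What is at stake is a figure that the protocol itself states: the number available to estimate and compare change in walking time, and the precision that goes with it. There is a related gap during follow-up. A participant who can walk at baseline and cannot at 12 or 24 months has no time in seconds at the later visit. Unless such participants are counted and shown, the reported change in walking time describes only those who could still do the test.

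**Working it through.** **Inputs.** From section 12.1: 500 enrolled, 225 per subgroup, 10% drop-out, SD of change 1.00 (no unit given), two-sided 95% confidence interval. From the exclusion criteria: non-ambulatory share strictly below 15%. Since 0.15 × 500 = 75, the largest permitted number is 74 (14.8%).

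**The protocol's own figure.** 500 × (1 − 0.10) = 450, and 450 / 2 = 225. It reproduces exactly, with drop-out as the only loss.

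**At the cap.** Able to walk at entry: 500 − 74 = 426. If drop-out is 10% among them, the evaluable number is 426 × 0.90 = 383.4, about 383. The shortfall is 450 − 383.4 = 66.6, about 67.

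- Loss shared between subgroups: 383.4 / 2 = 191.7, about 192 each.
- Loss wholly in the severe subgroup, assuming 250 enrolled in each: (250 − 74) × 0.90 = 158.4, about 158 severe, against 225 mild.

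**Most favourable overlap.** Suppose as many as possible of the 50 drop-outs (10% of 500) are also non-ambulatory. At the cap, 500 − 74 = 426 remain, still short of 450. With 50 or fewer non-ambulatory participants, complete overlap would leave 450 and no shortfall.

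**Precision.** The half-width for the difference between subgroups is 1.96 × SD × √(1/n₁ + 1/n₂), with SD 1.00.

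- As planned: 1.96 × √(2/225) = 0.185.
- At the cap, loss shared: 1.96 × √(2/191.7) = 0.200.
- At the cap, all in the severe subgroup: 1.96 × √(1/158.4 + 1/225) = 0.203.

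**Across the permitted range**, with 10% drop-out independent of ambulatory status:

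| Non-ambulatory | Evaluable | Per subgroup, loss shared | Half-width | Severe subgroup, all loss there (mild 225) | Half-width |
|---|---|---|---|---|---|
| 0 | 450 | 225 | 0.185 | 225 | 0.185 |
| 10 | 441 | 220.5 | 0.187 | 216 | 0.187 |
| 25 | 427.5 | 213.75 | 0.190 | 202.5 | 0.190 |
| 50 | 405 | 202.5 | 0.195 | 180 | 0.196 |
| 74 (cap) | 383.4 | 191.7 | 0.200 | 158.4 | 0.203 |

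For scale, keeping 450 evaluable walkers at the cap would take 450 / (0.90 × 0.852) ≈ 587 enrolled.

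**The case against.** The strongest reply is that the limit is a ceiling and not a forecast. The protocol gives no expected share, and if few non-ambulatory participants enrol the shortfall is trivial. This stands, and it is why the result is a range. A reader might infer that 225 per subgroup simply cannot be had; the protocol supports that only towards the cap.

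Second, the protocol neither defines non-ambulatory nor says that these participants skip the timed walk. That they have no score is inferred from a test done on foot from a standing start and scored in seconds. The inference is sound, but it remains an inference.

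Third, a reader might infer that the whole loss falls on the severe subgroup. That is plausible clinically, but section 12.1 neither defines the subgroups nor sets a quota for either. If they are formed among those who can walk, the loss is shared.

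Fourth, a reader might infer a loss of power. For a difference of 0.177 the calculation gives 46.7% at 225 per subgroup and 40.0% at 158 and 225. But section 12.1 states no power and presents its assumptions as concerning precision, so these are not departures from a stated target. The half-width is the fairer measure, and it worsens by about 10% at most (0.203 / 0.185 = 1.10).

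Fifth, a reader might infer that leaving out those who lose ambulation biases the standardized response mean downward. The protocol does not prescribe leaving them out, and scoring of an unable result may properly sit in the analysis plan. Nor is the direction established, since large losses raise both the mean and the SD of change. With assumed values, let 97% change by −0.075 m/s (SD 0.15, ratio 0.50 in absolute value) and 3% go from 1.0 to 0 m/s. The mean is 0.97 × (−0.075) + 0.03 × (−1.0) = −0.103. The variance is 0.97 × (0.0225 + 0.0056) + 0.03 − 0.103² ≈ 0.047, so the SD is about 0.216. The ratio is about 0.475: including them lowers it.

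Finally, grip strength, ADF strength and supine FVC need no walking, so three of the four key endpoints are untouched.

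**Conclusion.** The point holds as an unstated allowance in section 12.1, limited to the walking endpoint. The protocol's arithmetic is correct on its own terms but omits a loss that its eligibility note permits. At the cap, the evaluable number is about 383 instead of 450, and no more than 426 under the most favourable overlap with drop-out. The half-width for the subgroup difference goes from 0.185 to between 0.200 and 0.203.

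This rests on three assumptions: that non-ambulatory participants have no timed-walk score, that 10% drop-out applies equally to those who can walk, and that the SD of change is 1.00. The effect on precision is moderate. The point is worth correcting because the figure is stated for the endpoint that determines the sample size. It establishes neither a bias in the responsiveness statistics nor a confirmed deficit in the severe subgroup.

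**What to change.** In section 12.1, restate the evaluable number and half-width for the 30-foot go net of non-ambulatory participants, as a range: from 450 and 0.185 with none, to about 383 and 0.200–0.203 at the cap. Say which split between subgroups is assumed. State that 225 per subgroup applies only to the endpoints that need no walking: grip strength, ADF strength and supine FVC.

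For follow-up, add a case report form field recording that a participant was unable to do the walk, and why. Report the number who lose ambulation beside the change in walking time. Add a rank-based sensitivity analysis that places them as worst, without claiming in advance which way the standardized response mean would move.

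The cost is a few sentences in the protocol, one form field and one extra analysis. Enrolment, visits and the stated time endpoint stay as they are. Replacing time with speed and entering zero for those unable to walk is not needed here. It would change the endpoint to which 0.177 and 1.00 refer, and would not recover anyone non-ambulatory at baseline. The rank-based analysis does not recover them either, so the restated number is needed in any case.

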***Exclusion criteria for 60 participants in the muscle biopsy sub-study:***

- Known CTG repeat expansion size less than 100 repeats, unless there are clear cut signs of limb weakness and muscle wasting. This is in order to obtain a muscle tissue sample in a person more severely affected with myotonic dystrophy.
- Use of anticoagulant such as warfarin or a direct oral anticoagulant (e.g. dabigatran) due to the increased risk of bleeding.
- Use of aspirin or non-steroidal anti-inflammatory agents should be discontinued 3 days prior to the biopsy procedure, if possible.
- Platelet count <50,000 (if known) due to the increased risk of bleeding.
- History of a bleeding disorder due to the increased risk of bleeding.
- Advanced wasting of tibialis anterior (TA) muscle that precludes needle muscle biopsy in order to ensure that a sample taken would be of muscle and not just fat and fascia.
- Previous muscle biopsy of either TA in order to provide muscle tissue samples of non-biopsied (virgin) muscles.
  1. **Discussion of Subject Population**

Experienced investigators will be responsible for recruitment and follow-up of 500 subjects for this study. Participants will be men and women 18 to 70 with a positive genetic test for myotonic dystrophy type 1 or a clinical diagnosis of myotonic dystrophy type 1 (The clinical research criteria require myotonia, muscle weakness in a characteristic distribution, and history of similar findings in a first degree relative). Complete inclusion and exclusion eligibility criteria are listed above. To be eligible for enrollment into this study, subjects must meet all of the following eligibility criteria.

.

1. **SUBJECT IDENTIFICATION, RECRUITMENT AND CONSENT**
   1. **Method Of Subject Identification And Recruitment**

Volunteers will be recruited using local and nationwide recruitment tools. These individuals will be evaluated at one of the sites in the DMCRN. Recruitment media will include: recruitment websites and newsletters (e.g., Strong Health’s Clinical Trials website, the Muscular Dystrophy Association, and the Myotonic Dystrophy Foundation (MDF), clinicaltrials.gov, and direct mailings through the *National Registry of Myotonic Dystrophy and Facioscapulohumeral Dystrophy Patients and Family Members* (RSRB #12163).

## *4.1.a. Pre-entry Screening*

The study coordinator will make a provisional determination of ambulatory status and absence of exclusion criteria. Given that some patients who do not reside close to the study site will be recruited, the Investigator may elect to review a prospective participant’s medical records prior to Visit 1 in the study. . If this is necessary, subjects will be mailed a medical record release form for them to sign. Once the coordinator receives the signed release form they will request the medical records to review. Prospective participants who appear eligible will be scheduled for a Screening/Baseline Visit.

- 1. **Process of Consent**

The consent form will be mailed to the subject prior to the CRC visit so they have time to read the consent form and share the information with their family members. Informed consent will be obtained by the principal investigator or study coordinator after details of the study and its requirements have been presented, and there has been an opportunity for the participant to ask questions. Consent will be obtained only after complete information has been provided to the participant about the purpose of the study, the procedures, risks, benefits, contact persons, compensation, and care for injury, and voluntary participation. The participant and study personnel obtaining consent will sign the IRB approved consent form. The participant will receive a copy of the consent form after it has been signed. The original will be retained in the files of the investigator.

1. **METHODS AND STUDY PROCEDURES**
   1. Overview of Study Visits **(table 1)**

Obtain consent (30 minutes)

Medical history (15 minutes)

Patient reported outcomes (60 minutes)

Functional measures (90 minutes)

Electrocardiogram (10 minutes)

Blood draw (10 minutes)

| **Table 1. Schedule of EventsA** | | | | |
| --- | --- | --- | --- | --- |
|  | Baseline/0 month | 3 monthsB | 12 months | 24 months |
| **Medical History** | X |  | X | X |
| **Urine pregnancy testC** | X | X | X | X |
| **Vital signs** | X | X | X | X |
| **Physical exam** | X | X | X | X |
| **Myotonic dystrophy health index** | X | X | X | X |
| **Eat-10 questionnaire** | X | X | X | X |
| **Cogstate battery** | X |  | X | X |
| **Domain delta questionnaire** |  | X | X | X |
| **Quantitative myometry** | X | X | X | X |
| **Manual muscle testing** | X | X | X | X |
| **Iowa oral performance instrument** | X | X | X | X |
| **Forced vital capacity** | X | X | X | X |
| **Timed supine to sit** | X | X | X | X |
| **Timed up and go** | X | X | X | X |
| **10 Meter Walk/Run** | X | X | X | X |
| **4-stair climb** | X | X | X | X |
| **Step test** | X | X | X | X |
| **Grip strength** | X | X | X | X |
| **9-hole peg test** | X | X | X | X |
| **Picking up coins** | X | X | X | X |
| **Hand opening time and hand held myotonia instrument** | X | X | X | X |
| **Blood draw** | X |  | X | X |
| **Muscle biopsy (60 participants only)** | X | X |  |  |
| **Electrocardiogram** | X |  | X | X |

1. The order of procedures for the Clinical Evaluator is provided in Appendix 1.
2. The 3 month visit only pertains to the 60 participants in the muscle biopsy sub-study.
3. For women of childbearing potential

**Clinical Assessments**

- 1. Medical History

*Medical History.* A structured medical history will be used to capture phenotypes for the GWA study. Particular attention will be paid to age of onset. This information will be recorded on a specific CRF designed to ask questions in an open-ended fashion, followed by specific questions centered around the onset of myotonia, muscle weakness, cataracts, and cognitive or sleep symptoms. Common comorbidities will be documented. Specifically, sleep apnea, use of non-invasive ventilatory support or CPAP, presence of a pacemaker or ICD, history of bowel obstruction or pseudo-obstruction, and presence of thyroid disease or diabetes mellitus will be recorded.

*Urine Pregnancy Test.* Women of childbearing potential will have a urine pregnancy test. If the test is positive at the baseline visit, they will not be enrolled in the study. If the test is positive at the follow-up visits, the visit will be stopped and the participant will be asked to return at the next appropriate study visit that falls 6 months or later after delivery.

*Vital Signs.* Height, weight, blood pressure, pulse, respiratory rate, and temperature will be obtained at each study visit.

*Physical Exam.* An abbreviated physical exam will be performed by the study physician at each study visit.

- 1. Functional Measures
     1. *Upper Extremity Functional Outcome Measures*

*Grip Strength*. Participants will complete two trials of maximum hand grip using a JAMAR+ digital dynamometer on right and left hands. The maximum value will be recorded for each hand.

*Video Hand Opening Time and Handheld myotonia instrument.* To eliminate “warm-up” of myotonia the participants will rest the right hand for five minutes. The participant will squeeze the hand for three seconds then open the hand as quickly as possible. A video recording of the procedure will be obtained showing the forearm and hand but not the face. Recordings will later be assessed by a blinded reviewer to determine the hand opening time. Hand myotonia will also be assessed using a handheld force transducer, to determine the time required for isometric grip or pinch force to relax from 90% to 5% of peak force.

*Picking Up Coins*. Individuals will pick up 6 coins (one at a time) and hold them in their hand. The time to perform the task will be recorded.

*9-Hole Peg Test.* This test will be performed in accordance with standardized instructions. Two trials will be collected using the participant’s dominant hand. The best time and average will be recorded.

- - 1. *Measures of gait and mobility*

*10 meter walk/run*. From a standing start the participant will be asked to go 10 meters as quickly as possible, whether by walking or running. Orthotics and ankle braces are allowed. The time in seconds to complete the task will be recorded.

*4-Stair Climb.* Participants will be asked to climb up and down 4 stairs as quickly as possible, using steps with a six-inch rise and ten-inch run. Quality grades will be captured for this test to record the use of railings and manner of ascent (i.e., step-to or step-over-step pattern). The time it takes to complete the task will be recorded.

*Timed Up and Go*.Individuals are asked to rise from a chair, walk 3 meters, turn around, return to the chair, and sit. The time that it takes to complete the task will be recorded. Assistive devices, orthoses, and ankle braces will be allowed.

*Timed Supine to Sit*. Functional axial strength will be assessed by instructing individuals to move from supine to sitting on the edge of a plinth as quickly as possible. The time that it takes to complete the task will be recorded, as well as the manner of sitting (e.g., using one or two hands to pull up).

*Step Test*: This procedure is a test of dynamic standing balance. The participant will maintain stationary balance on one leg while the other foot steps rapidly on and off a 7.5 cm step. The score is the number of repetitions completed in 10 seconds. This test is designed to capture a larger dynamic range of disease progression in participants who are less severely affected, as it is less likely to have ceiling effects.

- - 1. *Measures of strength*

*Quantitative Myometry.* Quantitative Myometry Testing (QMT) will be performed using a force transducer attached to an inelastic strap as previously described. Standardized positions for isometric force testing will be used on five bilateral muscle groups: elbow flexors and extensors, knee flexors and extensors and ankle dorsiflexors.3 These muscles were selected for showing good test-retest reliability in our previous natural history studies.

*Manual Muscle Testing (MMT).* Manual muscle testing will be performed on 13 bilateral muscle groups (shoulder abductors, elbow flexors and extensors, wrist flexors and extensors, thumb flexors, hip flexors, extensors, and abductors, knee flexors and extensors, ankle dorsiflexors, and plantar flexors, plus neck extensor and neck flexors). Each muscle group will be scored using a modified MRC scale, in accordance with a protocol that standardizes the subject’s position, direction of movement, and joint angle for resistance, and the examiners stabilization and hand placement.

*Iowa Oral Performance Instrument (IOPI).* The IOPI consists of a pressure bulb attached to a manometer. The pressure bulb will be placed on anterior portion of the tongue and subjects are asked to push the bulb to the hard palate on the alveolar ridge just behind the upper central incisors for 3-5 seconds (repeated 3 times with a 30 second interval between trials). The average of the maximum pressure on three trials will be recorded. Buccal strength will also be quantified bilaterally with pressure bulb placed just inside the cheek. The subject will be asked to purse his/her lips to apply pressure to pressure bulb for 3-5 seconds for a total of 3 separate measures with 30 second rest period. The pressure bulb is single use and disposed of following the three trials.

*Spirometry.* Spirometry is performed in the sitting and supine position, to determine FVC, FEV1, and peak cough flow.

- 1. Patient Reported Outcome Measures

*Myotonic Dystrophy Health Index (MDHI*). The MDHI is a standardized questionnaire to quantify DM1-related symptoms and disease severity.

*Eating Assessment Tool (EAT-10).* The EAT-10 is a 10-item questionnaire designed to assess difficulties with swallowing or dysphagia.

*Domain Delta Questionnaire*. This questionnaire will evaluate the global rate of change, as well as changes in specific domains. Participants will be asked to report whether their health has: 1) Gotten a lot worse; 2) Gotten a little worse; 3) Stayed the same; 4) Gotten a little better; 5) Gotten a lot better. The average change in relevant outcomes will be compared among these five groups. This information will be used as an anchoring procedure to evaluate responsiveness and determine minimally important clinical difference. This questionnaire will be administered at the 12 and 24 month visits. It will also be administered at the 3 month study visit for participants in the biopsy sub-study.

*Work Productivity and Activity Impairment Questionnaire: Specific Health Problem V2.0 (WPAI:SHP).* This brief questionnaire will evaluate the impact of DM1 on a person’s ability to work.

*EQ-5D-SF*: This brief questionnaire will assess over health and impairment.

*Walking Scale-12*: This brief questionnaire will assess walking ability.

*DM1-Activ*: This questionnaire will assess impact of DM1 on daily life.

- 1. Cognitive function/CogState

This protocol will utilize a series of tests from the CogState, a computer-assisted method of cognitive assessment. The specific tests were selected to probe executive dysfunction that occurs in some DM1 patients, based on prior studies and input from neuropsychologists.

*Set-Shifting Test.* This test is a measure of executive function and cognitive flexibility. The participant is presented with a playing card and they have to guess if the card is a “target” card along two dimensions (color or a number). The software provides feedback to the participant and will not display a new stimulus until a correct response is given. The “target” stimulus dimension changes to either an intra-dimensional shift or to a different dimension (extra dimensional shift), and the participant is not told when the set-shifts will occur, and they are continuously required to relearn the target rule to proceed through the test. The multiple set-shifts within this test are pseudo-randomized to create alternate forms of the test. Participants are encouraged to work as quickly and as accurately as possible. The total number of errors is measured across five rounds; a lower score equals better performance.

*Detection Test.* The Detection Test uses a simple reaction time paradigm to measure processing speed. Participants are presented with a playing card on a screen and asked to respond “Yes” by pressing a button as soon as the card flips over to face up. Once a response has been made, the card goes to the back of the pack and a new card is presented. There is a learning period that involves a limited number of correct responses. The participant starts the actual test once the practice is completed. Participants are encouraged to work as quickly and as accurately as possible. Performance speed is measured. Lower scores equal better performance.

*One Back Test.* This is a test of working memory that uses an n-back paradigm. A playing card is presented to the participant facing up in the center of a screen. The participant must decide if the presenting card is identical to the previously presented card. Participants are asked to respond “Yes” or “No” accordingly. There is a practice period followed by the actual test. Participants are encouraged to work as quickly and as accurately as possible. Speed of performance is measured and reaction times are transformed for correct responses. A lower score indicates better performance.

*Identification Test.* This test measures attention by utilizing a choice reaction time paradigm. A card is flipped over face up. The participant must decide whether the card is red or not. If red, he/she presses the “Yes” key, and if not, he/she presses the “No” key. Participants are encouraged to press the appropriate key as quickly and as accurately as possible before the card flips over. Performance speed is measured. A lower score indicates better performance.

*Social-Emotional Cognition Test.* For this test, emotional recognition is measured using an odd-man–out paradigm. Participants are presented with a number of pictures on screen. One of the pictures is different in some way, and the participant must decide which image is different and tap it. Participants are encouraged to work as quickly and as accurately as possible. Accuracy of performance is measured. A higher score indicates better performance.

- 1. Biomarkers and muscle biopsy substudy

*Blood sample*. A blood sample will be collected at each visit to obtain plasma samples for biomarker discovery. The sample may be used to assess plasma RNA, metabolites, or proteins.

Blood tubes to be collected:

- *Yellow top* (8-10 ml) for DNA at baseline, 12 month, and 24 month study visits.
- *PAXgene tube* (2 tubes, 2.5 ml each tube, total 5 ml) for blood RNA at all three visits
- *Yellow top #2* (8-10 ml) for plasma at all three visits

Sample Processing:

*Yellow top* *for DNA.* The preferred method is that samples are placed in a -80 C freezer within two hours of collection. Samples may then be batch shipped to the University of Utah on dry ice. Alternatively, samples may be stored at 4 C for up to two days and then shipped overnight to the University of Utah.

*PAXgene tube*. Once collected, samples need to remain at room temperature for 2 hours. After this, samples may be stored in a -80 C freezer and then batch shipped to the University of Utah on dry ice.

*Yellow top #2*. Samples should be centrifuged for 10 minutes at 4000 RPM at 4 C immediately after collection. The supernatant (plasma) should be aspirated, divided into 3 aliquots, and stored in new tubes. The samples should be placed at -80 C immediately, then batch shipped to the University of Utah on dry ice.

*Urine sample.* The urine sample will be divided in two 5 ml tubes and stored at -80 C for batch shipping.

*Electrocardiogram (ECG).* This will be performed at each visit to evaluate the extent of cardiac conduction disease. PR interval and QRS duration will be determined using standard methods.

*Muscle biopsy sub-study*. The biopsy sub-study will examine RNA splicing defects that are characteristic of DM1. The proposed study builds on results from the initial DMCRN study, in which we obtained paired needle biopsy samples of tibialis anterior muscle from 97 patients. The samples were obtained 3 months apart to approximate the expected time course of muscle sampling in early-phase clinical trials. No significant safety issues were encountered. The biopsy procedure was well tolerated and > 95% of subjects who underwent the initial biopsy returned for the second biopsy. The second biopsy was obtained from the same leg, except in 19 patients whose second biopsy was obtained from the opposite leg. RNAseq of biopsy samples has now been completed and the preliminary analyses indicate that test-retest reliability of splicing biomarkers was substantially better for paired samples obtained from opposite legs. We seek now to confirm this finding in an independent cohort. Furthermore, in discussions with FDA officials about splicing biomarkers, the question was raised whether RNA splicing defects observed in tibialis anterior are representative of other muscles. Therefore, we are also testing whether splicing misregulation in an arm muscle, biceps brachii, is similar to that in tibialis anterior.

*Needle biopsy procedure.* 60 participants will undergo a muscle biopsy at the baseline visit and again at a three month study visit. The biopsy procedure is the same as our previous studies. After skin preparation using povidone-iodine or equivalent antiseptic, the skin and subcutaneous tissues will be anesthetized with 7-10 ml of 0.5% or 1% lidocaine, without epinephrine. The biopsy will be performed using side-cut biopsy needles, core biopsy needles, or the newer Vacora vacuum-assisted biopsy system. For side-cut needles (known as Bergstrom or UCHL needles) or Vacora 14 g biopsy probes, a 3‑mm incision will be made in the skin and muscle fascia, and muscle tissue will be obtained with 1 to 3 passes of the biopsy needle. Closure of the incision is obtained with steristrips or topical skin adhesive. For core biopsy needles (14 gauge, 10 mm length) a skin incision is not required, and 2 to 4 passes of the biopsy needle will be performed. Biopsy specimens (5 to 40 mg) will be frozen in liquid nitrogen within 2 minutes of removal, stored at -70C, and shipped in batches to the University of Rochester for targeted high-throughput RNA sequencing. A repeat biopsy will be obtained three months later from the opposite tibialis anterior (*n* = 40) or biceps (either side, *n* = 20). The site investigator will determine which site is used for the second biopsy, based on degree of muscle weakness and muscle atrophy. To enable comparisons across muscles having similar weakness, half of the biceps biopsies will be obtained from subjects having at least slight weakness of elbow flexors (MRC score ≤ 4+). Ultrasound may be used to guide needle biopsies of biceps, generally this is not necessary for tibialis anterior.

- 1. Genetic test for CTG expansion at the DM1 locus

Genomic DNA extracted at baseline will be analyzed by PCR, Southern blot, or both, to determine length of the CTG repeat as previously described.4 Repeat length may also be determined using higher resolution procedures as they become available. Repeat-primed PCR will be used to test for variant repeats (CCG or CGG repeats embedded within the CTG repeat tract) as previously described.5 DNA samples from the 12 and 24 month study visits may be used to assess test-retest reliability of repeat length measurements.

- 1. Genotyping procedure for GWAS

